**Inclusion criteria**
Patients aged 9-16 years, currently on the waiting list of one of the participating centersConsensus diagnosis of attention-deficit/hyperactivity disorder (ADHD) by 2 mental health care professionalsWritten informed consent provided by patients and their parents
**Exclusion criteria**
Patients with severe psychiatric conditions such as schizophrenia, bipolar disorder, or autism spectrum disorders, along with suicidal ideation or behavior (assessed by the Child Behavior Checklist Scale)Patients with no access to a smartphone or limited smartphone access (eg, patients in social facilities or those with low economic status)Patients with mild to severe mental retardation or deemed clinically unable to use the appPatients participating in special programs beyond standard care received while on the waiting listPatients not attending school (no homework)Patients in the titration period of methylphenidate or those with unstable doses over the past 3 months

### Study Design

The primary investigator’s center is the Department of Child and Adolescent Psychiatry at Nantes University Hospital Centre, which includes a clinical research unit in psychiatry, addictology, and child and adolescent psychiatry. The study will consist of a 3-month period with a randomized controlled trial design, where participants are divided into 2 parallel groups (group 1: care as usual or waiting list; group 2: PANDAH app). This is followed by a 3-month extension period (month 3 [M3] to month 6 [M6]), during which all participants will have access to the app (Figure 1). This second phase serves as an incentive for patients initially randomized into group 1. Assessments will be conducted at baseline (M0), M3, and M6 for each patient. Baseline evaluations will be performed by trained psychologists at inclusion and will include age, sex, school grade, treatment history, Child Behavior Checklist, Hamilton Anxiety Scale, ADHD Rating Scale, and Homework Performance Questionnaire (HPQ) [32] with parents. Interviews will last approximately 2 hours and 30 minutes, including instructions for using the app for group 2. Evaluations at M3 and M6 will be similar (2 hours and 30 minutes), allowing the assessment of the maintenance of effects and efficacy.

**Figure 1 figure1:**
[figure not shown]
Study design of PANDAH protocol. ADHD: attention-deficit/hyperactivity disorder; ASQ: Abbreviated Symptom Questionnaire; CDRS: Children’s Depression Rating Scale–Revised in Adolescents; HPC: Homework Problem Checklist; HPQ: Homework Performance Questionnaire; M: month; PANDAH: Programme d’Aide Numérique aux Devoirs pour Enfant avec TDA-H; PedsQL: Pediatric Quality of Life Inventory.

A screening visit will be scheduled for patients provisionally diagnosed with ADHD based on the psychologist’s interpretation of *Conners 3rd Edition* parents’ and teachers’ scales and ADHD Rating Scale V. The screening visit will involve evaluation by 2 health care professionals who will reach a consensus on the diagnosis. If the ADHD diagnosis is confirmed and the inclusion and exclusion criteria are met, participants will be fully informed about the study, their questions will be addressed, and consent (from both parents and children) will be obtained. For group 2 participants, the investigator will assist with setting up the app (15-20 minutes). Technical support will be provided remotely by each center from 8:00 AM to 6:00 PM via phone or email.

Given the unique attributes of our app, a traditional randomized controlled trial design proved unfeasible. Instead, we adopted a crossover design to facilitate a comparison between our app and a null intervention scenario. While this approach is likely to yield positive results, it may not definitively establish the specific efficacy of our intervention. Subsequent analysis will encompass the entire cohort, allowing for a comparison between those who used the app for 3 months and those who used it for 6 months. Any noticeable disparities may serve as an indicator of our intervention’s efficacy.

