**Methods:**

Individuals aged 9-16 years with an ADHD diagnosis and no comorbid psychiatric disorders are included. This is a multicenter study involving 9 reference centers for ADHD in France. The study comprises (1) a 3-month period with a randomized controlled trial design, where participants are divided into 2 parallel groups (group 1: care as usual or waiting list; group 2: PANDAH app), followed by (2) an extension period of 3 months (months 3-6), during which all participants will have access to the app. This second phase serves as a crucial incentive for patients initially randomly assigned to group 1. Assessments will be conducted at baseline, month 3, and month 6 for each patient by trained psychologists. The primary end point will be the global Homework Performance Questionnaire (HPQ), Parent version score at 6 months. The main analysis will adhere to the “intent-to-treat principle” (all patient data will be analyzed according to their initial group determined by randomization). We expect (1) HPQ score improvement in individuals using the app during the first 3-month period compared to individuals not using the app; (2) greater HPQ score improvement for individuals using the app for 6 months compared to those using the app for 3 months only; and (3) adherence to the PANDAH program, measured with in-app metrics.

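### The trial is labelled a crossover but is a parallel-group waiting-list trial with a delayed-start extension; its month-6 contrast compares 6 with 3 months of app use, not app with no app

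*Protocol article*

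**What the plan says.** Two descriptions of the design stand in the same section of the protocol article (Methods, Study Design).

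- Its opening paragraph, in agreement with the Abstract, describes "a 3-month period with a randomized controlled trial design, where participants are divided into 2 parallel groups", one on usual care or the waiting list and one on the app. A 3-month extension follows, "during which all participants will have access to the app".
- The last paragraph of the section, after Figure 1, says that a conventional randomised trial was not feasible and continues: "Instead, we adopted a crossover design to facilitate a comparison between our app and a null intervention scenario".

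That last paragraph then concedes of the approach that "it may not definitively establish the specific efficacy of our intervention". It goes on to a whole-cohort analysis "allowing for a comparison between those who used the app for 3 months and those who used it for 6 months", and closes with "Any noticeable disparities may serve as an indicator of our intervention’s efficacy".

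Three other places bear on how the M6 comparison is read:

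- Expected Findings lists app versus no app over the first 3 months as the first expectation, and a larger improvement with 6 than with 3 months of use as the second.
- Statistical Analysis bases the sample size on the parent-rated homework score (HPQ-P) at M3. It plans mixed models comparing the two groups, with an indicator for the control group's switch at M3.
- The Abstract states "The primary end point will be the global Homework Performance Questionnaire (HPQ), Parent version score at 6 months", whereas Secondary End Points lists the M6 score as secondary.

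**The concern.** In a crossover each participant, or each sequence group, receives both conditions in a different order. Here only the control group changes condition. The article therefore claims a randomised controlled design in one paragraph and disclaims it in another, although the randomised app versus no-app comparison at M3 is the strongest evidence the trial will produce.

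The closing sentence then turns to the M6 contrast for an indication of efficacy. No group is without the app at M6, so that contrast answers a different question from whether the app beats no app. If the efficacy conclusion leaned on it, a working app with an early plateau would go unrecognised. The word 'noticeable' also sets no bound on how large a difference must be before it counts.

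**Working it through.** **Step 1. The design, period by period.**

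| Period | Group 1 | Group 2 | Randomised contrast at the end |
|---|---|---|---|
| M0 to M3 | usual care or waiting list | app | app vs no app |
| M3 to M6 | app | app | 3 vs 6 months of app |

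Group 2 has no control period. This is a randomised, parallel-group, waiting-list design with a delayed-start extension.

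**Step 2. What each contrast estimates.** Let f(t) be the mean effect on the HPQ-P after t months of app use, with f(0) = 0. Assume the effect depends only on length of use. Time trends common to both groups cancel because the groups are randomised.

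- M3 contrast = f(3) − f(0) = f(3)
- M6 contrast = f(6) − f(3)

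| Scenario | f(3) | f(6) | M3 contrast | M6 contrast |
|---|---|---|---|---|
| Inert app | 0 | 0 | 0 | 0 |
| Full effect by 3 months, then plateau | 0.4 | 0.4 | 0.4 | 0 |
| Further gain d after 3 months | 0.4 | 0.4 + d | 0.4 | d |

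The first two rows give the same M6 contrast, so a null result at M6 cannot separate them; M3 can. If d is not 0, the app has some effect, because length of use cannot matter for an inert app.

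**Step 3. The plan's own sample size.** Inputs from Statistical Analysis: difference 0.4, SD 0.9, two-sided 5%, power 95%.

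n per group = 2 × SD² × (z₀.₉₇₅ + z₀.₉₅)² / difference² = 2 × 0.81 × (1.960 + 1.645)² / 0.16 ≈ 131.6, rounded up to 132, so 264 in total.

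The stated figure reproduces. The noncentral t calculation gives 132.5 per group, and power of 94.9% at 132 per group.

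**Step 4. The same sample applied to M6.** The article gives no M6 difference, so the values of d below are assumptions. SD 0.9 is carried over from M3, without baseline adjustment.

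SE = 0.9 × √(2/132) = 0.111. Power is from the two-sided t test at 5%.

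| Assumed M6 difference | Power, 132 per group | Power, 180 per group |
|---|---|---|
| 0 | 5% (false-positive rate) | 5% |
| 0.1 | 15% | 18% |
| 0.2 | 44% | 56% |
| 0.3 | 77% | 88% |
| 0.4 | 95% | 99% |

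The last column is shown because Recruitment gives a target of 360 (180 per group), while Statistical Analysis gives 264. For 95% power at d = 0.2 the total would be 1054.

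**Step 5. What chance alone produces.** With no true M6 difference and 132 per group:

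- P(|observed difference| ≥ 0.1) = 2 × [1 − Φ(0.1/0.111)] ≈ 37%
- P(|observed difference| ≥ 0.2) = 2 × [1 − Φ(0.2/0.111)] ≈ 7%

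**The case against.** The strongest reply is that the M6 contrast is still a comparison of randomised groups, analysed as randomised, which differ by design only in app access from M0 to M3. A statistically supported M6 advantage for group 2 would therefore be evidence against no effect. This stands. A reader might infer that the M6 contrast can show nothing about whether the app works; that goes too far. The limitation is asymmetric: a null result is uninformative about app versus no app, and a positive one is informative about earlier or longer use.

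The sentence is also hedged. It says that disparities may serve as an indicator, and it follows an admission that specific efficacy may not be established. It is not a decision rule, and nowhere does the article say that a null M6 result would count against the app. A reader might infer either; the text supports neither. The hedge does not cure the problem, though, because the M6 comparison is offered just after that admission as further evidence of efficacy.

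A reader might also fear that the crossover label leads to pooled before-and-after analyses of control children. No such analysis is planned: Statistical Analysis compares the two groups, with an indicator for the switch.

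On 'noticeable', Expected Findings supplies a direction and Statistical Analysis a model, and the test threshold can properly sit in an analysis plan not shown here. Step 5 shows only why the word cannot stand alone.

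Finally, the power figures are illustrative. Adjustment for baseline and use of repeated measures would normally raise them, and low power for a secondary contrast is not in itself a fault. The Abstract's placing of the primary end point at 6 months is a separate inconsistency, and this point does not depend on it.

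**Conclusion.** The point holds in two parts.

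1. **The label is wrong.** It contradicts the parallel-group description in the same section and in the Abstract, and it understates the randomised comparison the trial contains.
2. **The sentence on M6 should be narrowed.** The contrast estimates f(6) − f(3). Its expected value is 0 for an app whose effect is complete by 3 months, so absence of a difference says nothing about app versus no app. A supported difference favouring group 2 indicates an early-start or duration effect.

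The sample size is built on 0.4 at M3. At M6, power is about 15%, 44% and 77% for differences of 0.1, 0.2 and 0.3. Those figures rest on three assumptions: the M6 differences themselves, an SD of 0.9 carried over from M3, and an unadjusted test with 132 per group and no loss to follow-up. The conclusion about what M6 estimates does not depend on them.

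The change is worth making because it ties the efficacy conclusion to the contrast the trial was sized for.

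**What to change.** In Study Design, remove the crossover label and the statement that a conventional randomised trial was not feasible. Describe the design as randomised, parallel-group, waiting-list controlled for 3 months, with a delayed-start extension from M3 to M6.

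Replace the closing sentence of that section with:

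> Efficacy of the app versus no app is judged on the randomised M3 HPQ-P contrast. The M6 contrast between randomised groups is a secondary estimate of 6 versus 3 months of use, reported with its 95% CI; absence of an M6 difference is not evidence against efficacy, and a difference favouring group 2 supports an early-start or duration effect.

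The time point of the primary end point in the Abstract would have to be brought into line with this text.

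The cost is wording only. Visits, measurements and sample size need not change for this point. The sponsor gives up M6 as a stand-alone argument for efficacy.

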### Intervention

The intervention is based on the PANDAH app, which engages patients in understanding their grades, homework location, surrounding environment, habits, schedules (including sports and therapy), and expectations. PANDAH guides students throughout their homework sessions, from ensuring they have everything they need to create a comfortable workspace to packing for the next day. During sessions, patients receive positive feedback and reinforcement when appropriate. The app also provides personalized artificial intelligence–enhanced advice, such as suggesting students tackle challenging subjects first to reduce anxiety and avoid extended sessions. PANDAH is used independently at home but is complemented by real-life sessions (3 times a year during the school term) to familiarize children and adolescents with the app and address any questions (Figure 2).

Usage during the study will be monitored in terms of time, frequency, and schedule, with in-app data securely transferred to the principal investigator for analysis.

**Figure 2 figure2:**
[figure not shown]
Screenshots and general concept of the PANDAH app. ADHD: attention-deficit/hyperactivity disorder; PANDAH: Programme d’Aide Numérique aux Devoirs pour Enfant avec TDA-H.

### Primary End Point

The primary end point will be the global score on the HPQ, Parent version (HPQ-P) [32]. This 12-item questionnaire, developed in partnership with parents using focus groups and interviews, uses a 4-point scale.

### Secondary End Points

The secondary end points include (1) global and domain scores of HPQ-P at M6 [32]; (2) global and domain scores of HPQ, Teacher version at M3 and M6 [32]; (3) Patient Pediatric Quality of Life Inventory and Pediatric Quality of Life Inventory Family Impact Module at M3 and M6 [33,34]; (4) global score of Homework Problem Checklist for Parents at M3 and M6 [35,36]; (5) Inattention and Hyperactivity scores from Conners 3 at M3 and M6 ; (6) in-app scores for fill rate and number of complete app sessions during the M0-M3-M6 period; (7) Children’s Depression Rating Scale–Revised in Adolescents and Hamilton Anxiety Scale at M3 and M6; and (8) Likert scale for teachers at M3, M6, and end of the academic year (Mx) regarding changes in students’ academic levels: “Degraded/Slightly Degraded/Slightly Improved/Improved” [37].

Secondary criterion 6 will further allow us to assess the actual usage of the app by estimating the time the app is open and the time of interaction (using fingers) with the app. This way, we can evaluate whether the child is not solely focused on the app but engaged in other activities as well.

### Safety

Data security is a crucial aspect of digital tools. Most data will be stored on the user’s smartphone and inaccessible to unauthorized individuals without the user’s personal code. Notably, the app does not require an internet connection to function. Patients included in the research will transfer data securely to investigators using a multistep process, ensuring encryption and secure handling. The data will be decrypted and analyzed only by the principal investigator. Data will be securely stored and analyzed in a Microsoft Excel spreadsheet.

### Statistical Analysis

The primary analysis will adhere to the “intent to treat principle,” analyzing all patient data based on their initial group determined by randomization.

Descriptive statistical analyses will be conducted for categorical data (number and percentage) and continuous data (range, mean, median, and IQR).

Confirmatory factor analysis will be applied preliminarily to the HPQ-P and HPQ, Teacher version questionnaires to assess construct validity. Adequate fit will be considered if the Comparative Fit Index≥0.90 and the root mean square error of approximation≤0.08. Meaningful differences between well-fitting models will be assessed using Δ Comparative Fit Index>+0.01. Reliability will also be assessed using Cronbach α, considered satisfactory if above 0.7.

Cross-sectional comparisons (eg, M3) of continuous and categorical data will use linear or logistic regression, adjusting for M0 if appropriate based on the data collection schedule.

Longitudinal data will be analyzed and compared between the 2 groups using linear mixed models with random effects to account for repeated measurements within patients. Different models, including random intercept or slope models, will be assessed based on the Akaike information criterion, and normality and homoscedasticity of residuals will be examined. A dummy variable reflecting the switch at M3 from the control group to the PANDAH app group will be included in the models (M0 to M6).

Assuming a mean difference of 0.4 on the global score of the HPQ-P at M3 between the 2 groups, with a common SD of 0.9, a total of 264 patients (n=132, 50% in each group) is required to detect this difference with a 5% type I error and 95% power in a 2-tailed *t* test. Assuming 0 attrition (no loss to follow-up) due to proximal assessments at M3, saturation of the child psychiatrist network, and no removal or relocation of families shortly after the school year begins, our aim is to include precisely 264 patients in the PANDAH trial.

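### With three fixed visits, choosing the longitudinal model's random effects by AIC can misstate the standard errors of between-group effects read from that model; an unstructured covariance avoids this at almost no cost (low severity)

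*Protocol article*

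**What the plan says.** All references are to the protocol article.

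- **Visits** (Study Design): "Assessments will be conducted at baseline (M0), M3, and M6 for each patient".
- **Longitudinal model** (Statistical Analysis): "Longitudinal data will be analyzed and compared between the 2 groups using linear mixed models with random effects". The form is then left to the data: "Different models, including random intercept or slope models, will be assessed based on the Akaike information criterion". Residual normality and homoscedasticity are to be examined, and a dummy marks the control group's move to the app at M3. No unstructured covariance and no robust standard error is named.
- **Single-visit comparisons** (same section): these go to linear or logistic regression, with M3 as the example, adjusted for M0 where appropriate.
- **Sample size** (same section): the starting point is "Assuming a mean difference of 0.4 on the global score of the HPQ-P at M3 between the 2 groups". Both arms are given an SD of 0.9, and the result is 132 per arm, 264 altogether, for a two-tailed t test at 5% with 95% power and no attrition.

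**The concern.** A random intercept forces one variance at all three visits and one correlation between every pair. A random linear slope forces a variance that is quadratic in time, with a single residual variance. It also forces the M0-M3 change and the M3-M6 change to have the same variance. Real scores may do otherwise: the spread at entry may differ from later, or M3 and M6 may correlate more closely than M0 and M3.

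With complete data and group-by-visit means, the covariance choice leaves the estimated M3 difference and the change from M0 alone but sets their standard errors. At stake are the interval and p value of between-group effects taken from the mixed model. AIC keeps the better-ranked candidate; it does not show that this candidate is adequate. The residual check may reveal unequal variances but does not examine the correlations between visits.

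**Working it through.** **1. The plan's own figure.** Inputs from the Statistical Analysis section: difference 0.4, SD 0.9, two-sided 5%, power 95%.

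n per arm = 2 × (1.960 + 1.645)² × 0.9² / 0.4² = 2 × 12.996 × 0.81 / 0.16 = 131.6, so 132 per arm and 264 in total. The stated figure reproduces. The noncentral t gives 94.92% power at 132 and reaches 95% at 133, which is immaterial. This calculation involves no random effects.

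**2. Counting parameters.** Three visits give 3 variances + 3 covariances = 6 elements. Random intercept: 2 parameters. Intercept plus slope: 4. Unstructured: 6.

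**3. From a wrong standard error to type I error.** If the model's variance for a contrast is Vm and the true one is Vt, a nominal 5% test rejects under the null with probability 2 × [1 − Φ(1.96 × √(Vm/Vt))]. The visit SDs and correlations below are assumptions. Correlations are given in the order M0-M3 / M3-M6 / M0-M6.

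*Random intercept, M3 difference.* The fitted variance is the mean of the three visit variances.
- SD 0.8/1.0/0.8, all correlations 0.5: Vm = (0.64 + 1.00 + 0.64)/3 = 0.76 against Vt = 1.00. √0.76 = 0.872; 1.96 × 0.872 = 1.709; type I error 8.8%.
- SD 0.9/0.75/0.9, all correlations 0.5: Vm = (0.81 + 0.5625 + 0.81)/3 = 0.7275 against Vt = 0.5625. √1.293 = 1.137; 1.96 × 1.137 = 2.229; type I error 2.6%.

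AIC keeps the random intercept in both.

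*Random slope, change from M0 to M3, SD 0.9 throughout.* The fitted variance is the mean of the two three-month change variances, each 2 × 0.81 × (1 − correlation).
- Correlations 0.5/0.7/0.5: true variances 0.81 and 0.486; Vm = 0.648. √(0.648/0.81) = 0.894; 1.96 × 0.894 = 1.753; type I error 8.0%.
- Correlations 0.4/0.8/0.4: true variances 0.972 and 0.324; Vm = 0.648. √(0.648/0.972) = 0.816; 1.96 × 0.816 = 1.600; type I error 11.0%.

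AIC favours the slope model in both.

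**4. AIC-selected model, wider set (264 patients, complete data).**

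| Assumed truth | Contrast | Type I error |
|---|---|---|
| Compound symmetry, 0.5 or 0.7 | change; baseline-adjusted M3 | 5.0-5.1% |
| AR(1), 0.5-0.8 | change from M0 | 5.0-5.2% |
| AR(1), 0.5-0.8 | baseline-adjusted M3 | 5.8-6.4% |
| SD 0.9, correlations 0.7/0.7/0.5 | M3 difference | 6.1% |
| M0 SD 0.80-0.85, then 0.9 | M3 difference | 5.4-7.0% |
| SD 0.7/0.9/0.9, correlations 0.7/0.7/0.5 | M3 difference | 7.8% |
| SD 0.8/1.0/0.8, correlations 0.7/0.7/0.5 | M3 difference | 9.3% |
| SD 0.9/0.75/0.9, correlations 0.7/0.7/0.5 | M3 difference | 3.6% |
| SD 0.9/0.7/0.9, all correlations 0.5 | baseline-adjusted M3 | 2.6% |

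Under compound symmetry AIC picked the slope model in about 7% of draws and the error stayed at 5.0-5.1%. The harm therefore comes from candidates that do not fit, not from the act of selecting.

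**5. Effects that are largely spared.** An app on/off dummy stayed at 5.0% in the scenarios tried when visit and group terms were also in the model; without the group term it ranged from 4.2% to 7.6%. The M0-to-M6 change often stayed near 5%.

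**6. The M3 regression.** Linear regression at M3 adjusted for M0, 20,000 simulated trials in each of four settings: 5.2-5.3% (Monte Carlo standard error about 0.15 points), which is nominal for practical purposes.

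**The case against.** The strongest objection is that the article assigns single-visit comparisons such as M3 to regression and sizes the trial on a t test at M3. A reader might infer from the table that the trial's M3 test runs above or below its 5% level. The documents do not support that: neither method uses the random-effects covariance, and step 6 confirms it for the regression. This objection stands, and it limits the point to effects read from the longitudinal model. That model still matters, because it is a stated between-group comparison. The article also does not settle which analysis gives the primary result: the abstract places the primary end point at 6 months, the sample size is for M3, and HPQ-P at M6 is also listed as secondary.

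Second, the sizes are assumed. A reader might take a definite inflation from them, but the article gives only SD 0.9 and no correlations. The largest M3-difference errors need an SD that rises or dips at M3 alone, which nothing in the article suggests. This also stands.

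Third, the candidate list is open, so an unstructured covariance is not excluded. True, but it is not promised either, and an open list settled on the trial data fixes less than a closed one.

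Fourth, AIC selection is common practice, and covariance details often sit in the SAP. An omission would be no finding here. The article, however, states a rule, and a better one is available for three visits.

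**Conclusion.** The point holds for between-group effects read from the longitudinal mixed model, and only there. The two named random-effects forms cannot represent a general three-visit covariance, and AIC does not repair that, so standard errors can err in either direction. Under assumed covariances, the type I error of an M3 contrast from this model is about 5% under compound symmetry, about 5.5-7% under mild departures and about 2.6-11% under stronger ones. These are illustrations, not bounds, and they assume 132 per arm, complete data and group-by-visit means. The change from M0 under AR(1), and an app on/off dummy alongside visit and group terms, stay at or near 5%. The M3 regression and the t test are unaffected. Severity is low: a cheap improvement to a stated rule, not a threat to the M3 comparison on which the trial is sized.

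**What to change.** Replace the AIC sentence with, for example: *The longitudinal model treats visit as categorical and uses an unstructured within-patient covariance for M0, M3 and M6, fitted by REML with Kenward-Roger degrees of freedom. Random effects are not chosen from the data. If this model does not converge, a random-intercept model with robust standard errors is used.* The switch dummy can stay in the mean model.

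With all 6 covariance elements estimated, an M3 contrast has a type I error of about 5% whatever the true covariance (theory, not simulated). The cost is 6 − 4 = 2 to 6 − 2 = 4 more covariance parameters, negligible with 264 patients. Design, sample size and data collection do not change. The trial is ongoing, so the sentence should be settled before the data are analysed.
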